**Outcomes**

Primary outcome:

**1)** To characterize the association between Shear-Wave Elastography (SWE) and other US markers (thickness and thickness fraction for the diaphragm, echogenicity and cross-sectional area for the peripheral muscles).

As secondary outcomes:

**2.a)** The association between the changes in DUS and PMUS over time (between different times points and first assessment at ICU admission) will also be explored using change in all US markers.

**2.b)** The analysis of a combined model of one DUS marker and one PMUS marker (multiple combinations will be performed between all markers) to predict weaning success/failure will be performed as well.

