**Measurements and procedures**

Study visits will be performed as follows:

- at **24 hours of ICU admission**
- **daily until day 5**, then
- **weekly** (at the end of every 7 days period),
- **at the extubation time**,
- at **ICU discharge**.

At each of these time points, we will assess quadriceps *rectus femoris* (RF) and diaphragm muscles (bilaterally), through PMUS and DUS measurements, respectively; while intubated and ventilated, the patient’s airway occlusion pressure (P0.1) will be monitored and recorded using the patient’s ventilator. In addition, for all time-points, patients’s ability to collaborate will be “checked” with “awakening” criteria by using the Standardized Five Questions (S5Q). If this ability to collaborate is confirmed, a Medical Research Council (MRC) sum score assessment will also be performed. Screening and assessments for each time-point will be performed without interfering with sedation/neuromuscular blocking agent medical administration.

**Number of Participants AND Rationale:** 84 participants.

For rationale, please see section “Statistical Considerations”, here bellow.

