**Statistical Considerations:**

Changes over time in DUS markers, PMUS markers and MRC sum score will be explored using repeated-measures analysis of variance (ANOVA) or the Friedman test. For each time-point, association between different DUS or PMUS marker (DUS *versus* DUS or PMUS *versus* PMUS) will be analysed using *Pearson’s* or *Spearman’s Rank-Order* correlations tests; associations between DUS and PMUS (one DUS to one PMUS markers), will be assessed as well. Bland-Altman analysis will be performed to quantify the agreement (diagnostic accuracy) between US techniques for each structure.

In the prediction of weaning success and the presence of ICU-Acquired Weakness (ICUAW), logistic regression models will be performed taking into account the percentage of change (in relation to ICU admission values) and the absolute values of DUS markers alone, PMUS markers alone, and combined DUS and PMUS markers; these models will be adjusted for measured covariates (when available). Furthermore, discriminative power of all ultrasonographic techniques to detect weaning/failure will be assessed using Receiver Operating Characteristics (ROC) curves and Area Under the Curve (AUC) calculations.

Sample size estimation

For these analyses, we aim to be able to identify a linear correlation between the two US markers (SWE and one CMUS) and between the 2 muscles examined for each time-point. For that, we estimated a medium effect size of 0.30 for Pearson’s r, as proposed by Cohen. To reach the power to identify such an association with 80% power, an alpha level of 5% and a 2-sided test, we would need to include a minimum of **84 participants**.

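### At extubation and ICU discharge, an unadjusted correlation of diaphragm change with limb-muscle change can partly reflect how long each patient was ventilated or stayed

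*Protocol*

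**What the plan says.** Three parts of the Protocol bear on this.

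- **Measurements and procedures** scans both muscles at every visit. The 24-hour, daily (to day 5) and weekly visits fall on set days. Two further visits are set by events: one "at the extubation time" and one at ICU discharge.
- **Outcomes**, under item 2.a of the secondary list, states: "The association between the changes in DUS and PMUS over time (between different times points and first assessment at ICU admission) will also be explored". Every ultrasound marker is to enter as a change.
- **Statistical Considerations** names Pearson or Spearman correlation, time-point by time-point, for pairs of markers within a muscle. For pairs across muscles it adds that "associations between DUS and PMUS (one DUS to one PMUS markers), will be assessed as well". The sample size paragraph likewise aims at a correlation "between the 2 muscles examined for each time-point".

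Covariate adjustment is mentioned only in the sentence on the logistic models for weaning and ICU-acquired weakness. Nothing in the correlation text refers to days since the first scan.

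**The concern.** At a fixed-day visit every patient has had the same time to change. At extubation or discharge, one patient may have had a few days and another several weeks. If both markers drift on average, long-course patients show large changes in both and short-course patients show small changes in both. That alone produces a positive correlation, even when a patient's rate of diaphragm change says nothing about the rate of limb change.

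The study's title asks about the relationship of the two muscles over time. A correlation that mixes this relationship with length of course could be read as support for a link. It also does not measure the same thing as the correlations at fixed days.

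**Working it through.** **1. The plan's own figure.** Inputs from Statistical Considerations: "we estimated a medium effect size of 0.30 for Pearson’s r, as proposed by Cohen", "an alpha level of 5% and a 2-sided test", and 80% power. Fisher z gives n = ((1.960 + 0.842) / atanh 0.30)² + 3 = (2.802 / 0.3095)² + 3 = 84.9. With the usual bias correction it is 83.98. The stated 84 reproduces, so the sample size arithmetic is not at issue. It gives r = 0.30 as the yardstick.

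**2. Algebra.** Let T be days since the first scan. Let the change be a·T + error in the diaphragm and b·T + error in the limb muscle, where a and b are patient-specific daily rates. If a, b, T and the errors are all independent:

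- Cov(changes) = mean(a) × mean(b) × Var(T)
- Var(change) = mean(rate)² × Var(T) + SD(rate)² × E(T²) + error variance

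On a fixed day Var(T) = 0, so the covariance is zero. At an event-driven visit it is positive if both means are non-zero with the same sign, and zero if either mean is zero.

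**3. Central case.** The Protocol gives no rates, measurement error or spread of stay, so all of these are assumptions: mean loss 1.5 and 1.0 %/day, between-patient SD of rate 1 %/day, error SD 8% of baseline, extubation day lognormal with median 8 and log-SD 0.6, and T = day − 1.

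- Mean day = 8 × exp(0.18) = 9.58; Var(T) = 9.58² × (exp(0.36) − 1) = 39.8
- E(T²) = 39.8 + 8.58² = 113.3
- Cov = 1.5 × 1.0 × 39.8 = 59.6
- Variances: 2.25 × 39.8 + 113.3 + 64 = 266.8, and 39.8 + 113.3 + 64 = 217.1
- r = 59.6 / √(266.8 × 217.1) = 0.25

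**4. Simulation with unrelated rates, 60 patients at the visit.**

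| Setting | Mean r | Pearson p < 0.05 | Spearman p < 0.05 |
|---|---|---|---|
| Fixed day 5 | 0.00 | 5% | – |
| Extubation, central case | 0.24 | 48% | 27% |
| Extubation, low end | 0.08 | 15% | 8% |
| Extubation, high end | 0.40 | 81% | 66% |
| Loss stops 10 days after first scan | 0.04 to 0.11 | 6% to 15% | – |
| No average change in one muscle | 0 | – | – |

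The low and high ends span rate SD 0.75 to 1.5 %/day, error 8 to 12%, median day 7 to 10 and log-SD 0.5 to 0.7. A second set of assumptions (84 patients, mean loss 1 and 1.5 %/day, error 5 to 10 points, log-SD 0.3 to 0.7) gives mean r from 0.04 to 0.53.

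**5. Does removing elapsed days help?** Without a plateau, and with T independent of the rates, the mean partial r is about 0.00. Partial Pearson with the ordinary t test still rejects in 5% to 20% of samples in the 60-patient settings, because the spread of change grows with T. Partial Spearman rejects in 5% to 6%. With a plateau, linear adjustment leaves r of about 0.04, and partial Spearman still rejects in about 5%.

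**6. If wasting itself delays extubation.** Let log-day correlate 0.5 with each rate in the central case. The unadjusted mean r rises to 0.51. Partial Pearson averages about −0.14 (26% rejecting) and partial Spearman about −0.06 (8%). With correlations of −0.3, the unadjusted r falls to about 0.00.

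**The case against.** The strongest reply is that the faulted analysis is assembled from two sections. The correlation sentence does not mention change, and outcome 2.a names no method. Which visits enter 2.a, and whether days are removed, could be settled in a statistical analysis plan. This lowers the severity but does not dispose of the point: the only association method in the Protocol is a per-time-point correlation, extubation and discharge are among its time-points, and following the text gives the unadjusted analysis.

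A second reply is that, at extubation, whether patients with more limb loss also have more diaphragm loss is a fair descriptive question with a genuinely non-zero answer. That stands. The unadjusted value is not wrong as a description; it is open to misreading as evidence that the two rates of change are connected. The fix therefore keeps it and labels it.

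Third, the model treats time to extubation as unrelated to wasting, whereas the Protocol expects the markers to relate to weaning. That also stands: both the artefact and the adjusted value depend on a relationship the documents do not give.

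A reader might infer that two independently wasting muscles are bound to appear linked at these visits. The documents do not support that. They state no rate, no length of stay and no direction of change for stiffness, thickness fraction or echogenicity, and the artefact vanishes if one marker has no average change. Nor does the Protocol plan any comparison between event-driven and fixed-day correlations.

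**Conclusion.** The concern holds in a limited form. At extubation and ICU discharge, the unadjusted correlation of change mixes any real link between the muscles with differences in elapsed time, provided both markers change on average. Its existence under that condition is algebra; its size cannot be found from the documents. On the main set of assumptions mean r runs from about 0, through about 0.1 with a plateau and 0.24 centrally, to about 0.4. The upper part exceeds the 0.30 the study is sized to detect, but only under the assumed rates and spread of stay.

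The reach is narrow: an exploratory secondary outcome at two visits. It would be wrong to extend it to the primary outcome, which relates elastography to the other ultrasound markers; to the fixed-day and weekly visits, where elapsed time is common to all; or to the figure of 84. It would also be wrong to present partial correlation as a complete cure, given step 6. Low to moderate severity; a cheap improvement.

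**What to change.** In Statistical Considerations, state that:

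- the correlations of change for outcome 2.a are read mainly from the fixed-day visits, for example day 5 and day 7;
- at extubation and ICU discharge, a partial Spearman correlation removing days since the first scan is reported beside the unadjusted value;
- the unadjusted value at these two visits includes the effect of elapsed time and is not compared with fixed-day correlations;
- if wasting itself delays extubation or discharge, the adjusted value can be biased slightly downwards.

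The cost is wording only. Days since the first scan follow from the visit dates, so no new data or visits are needed. The downside is one degree of freedom and a probably smaller reported correlation at these two visits.

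### Bland-Altman agreement is planned between ultrasound markers that measure different quantities, and is equated with diagnostic accuracy; the result cannot be interpreted, although the primary association analysis does not depend on it

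*Protocol*

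**What the plan says.** The primary outcome in the protocol's Outcomes section is "To characterize the association between Shear-Wave Elastography (SWE) and other US markers". It names the other markers as "thickness and thickness fraction for the diaphragm, echogenicity and cross-sectional area for the peripheral muscles".

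Statistical Considerations then gives two analyses that compare markers within a structure:

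- Correlation. "For each time-point, association between different DUS or PMUS marker" is to be examined with Pearson's or Spearman's coefficient.
- Agreement. "Bland-Altman analysis will be performed to quantify the agreement (diagnostic accuracy) between US techniques for each structure".

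The sample size in the same section rests on correlation alone: "we estimated a medium effect size of 0.30" for Pearson's r, "with 80% power, an alpha level of 5% and a 2-sided test", and hence "we would need to include a minimum of 84 participants".

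The protocol describes no second rater, no repeat acquisition, no second method for any single marker, and no conversion of the markers to a common scale.

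**The concern.** Bland-Altman analysis studies the difference between two measurements of the same quantity. Its bias and limits mean something only if that difference does. No two markers listed for the same structure measure the same thing, so a difference such as stiffness minus thickness has no physical meaning, and its size is set by the choice of unit.

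The same sentence treats agreement as if it were diagnostic accuracy. Accuracy is a property of a test against a reference condition, and none is named there.

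What is at stake is the interpretation of the results. Limits computed this way could be reported as SWE failing to agree with conventional ultrasound when the two were never expected to give the same number. They could also be presented as evidence of accuracy when they are not.

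**Working it through.** **1. The plan's own figure.** Inputs from Statistical Considerations: r = 0.30, 80% power, two-sided 5%. By Fisher's z, n = ((1.960 + 0.842)/atanh(0.30))² + 3 = 84.93, which rounds up to 85. At n = 84 the power is 79.6% by plain Fisher z and 79.96% with the bias-corrected version. The stated 84 is reproduced to within one participant, so sample size is not at issue.

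**2. The pairs the sentence can refer to.**

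| Structure | Markers (Outcomes) | Nature of the quantity |
| --- | --- | --- |
| Diaphragm | SWE; thickness; thickness fraction | stiffness; length; ratio |
| Rectus femoris | SWE; echogenicity; cross-sectional area | stiffness; image brightness; area |

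Each structure gives three pairs, and none of the six pairs shares a quantity. The protocol states no units; that they differ follows from what is being measured.

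**3. Dependence on the unit.** The protocol gives no means or SDs, so these are assumed for illustration: SWE mean 20, SD 5 (kPa); thickness mean 2.0 mm, SD 0.5 mm; r = 0.30 as in the sample size section.

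Limits = (m₁ − m₂) ± 1.96·√(s₁² + s₂² − 2·r·s₁·s₂)

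- Thickness in mm: 18 ± 1.96·√(25 + 0.25 − 1.5) = 18 ± 1.96·4.87, giving 8.4 to 27.6.
- Thickness in cm: 19.8 ± 1.96·√(25 + 0.0025 − 0.15) = 19.8 ± 1.96·4.99, giving 10.0 to 29.6.
- Thickness in micrometres: −1980 ± 1.96·√(25 + 250000 − 1500) = −1980 ± 1.96·498.5, giving −2957 to −1003.
- Thickness in tenths of a millimetre (20±5): 0 ± 1.96·√(25 + 25 − 15) = 0 ± 1.96·5.92, giving −11.6 to 11.6.

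The patients and the association are the same throughout, yet the bias is positive, negative or zero according to the unit.

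**4. Perfect correlation.** At r = 1 the SD of the difference is |s₁ − s₂|. In mm it is 4.5, so the limits are 18 ± 8.82, or 9.2 to 26.8. In tenths of a millimetre it is 0 and the bias is 0, which would read as perfect agreement. The verdict on agreement is decided by the unit.

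**5. Standardising first.** If both markers are z-scored, the bias is 0 by construction and the limits are ±1.96·√(2(1 − r)):

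- r = 0.30: ±2.32 SD
- r = 0.50: ±1.96 SD
- r = 0.90: ±0.88 SD

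The limits are a function of r alone and add nothing to the correlation already planned.

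**The case against.** **The sentence lists no pairs and no scale, and a separate SAP may define both.** This is fair: the cross-marker reading is an inference. But the sentence compares techniques within a structure, comes directly after the sentences on associations between markers, and the protocol offers no repeat or second-rater reading as an alternative. A SAP could choose a scale, but no scale makes stiffness and thickness the same quantity. If a valid use was intended, the wording still has to change.

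**Percentage change from ICU admission is dimensionless and appears in the plan.** It would remove the dependence on kPa, mm or cm. However, the protocol assigns it to the logistic models, not to this analysis, and a percentage change in stiffness is still not a measurement of the percentage change in thickness.

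**Both muscles are scanned on both sides, so left against right could be compared.** Two sides are not two techniques. The difference would include true anatomical asymmetry, so it would not be agreement between methods.

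**The impact is small.** This stands in large part. A reader might infer that the primary analysis is invalid because the pairs are those of the primary outcome. The documents do not support that: the primary outcome is association, correlation is the method named for association, and the sample size rests on r. A reader might also infer that the analysis would always show bias. It would not; as shown above, a suitable unit brings the bias to zero.

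**Conclusion.** The sentence is wrong as written, on two counts. Bland-Altman between the listed markers gives a bias and limits that cannot be interpreted and that change with the unit, and agreement is not diagnostic accuracy.

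The error is confined to this one analysis. The primary association analysis, the 84 participants, the logistic models and the ROC analyses all stand without it. The harm lies in reporting: a false conclusion that SWE does not agree with conventional ultrasound, or an accuracy claim with no reference condition behind it.

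The numerical limits rest on assumed means and SDs and only illustrate the point. The conclusion does not depend on them. It rests on reading the techniques for each structure as the markers listed under Outcomes.

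**What to change.** - Delete Bland-Altman analysis between different markers.
- Delete the parenthetical that equates agreement with diagnostic accuracy.
- For SWE against each other marker of the same muscle, rely on the correlations already planned and report each with its 95% CI.
- Use Bland-Altman only if repeat or inter-rater readings of the same marker on the same muscle exist. The protocol describes none, so name them if they are collected.
- Reserve accuracy language for the ROC/AUC analyses of weaning.

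The cost is a revision of one sentence. No new data are needed, and nothing is lost except an output that could not be interpreted.

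### Ultrasound markers are related to muscle strength only through a yes/no weakness outcome, although the graded MRC sum score is already collected and would give a more powerful exploratory analysis

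*Protocol*

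**What the plan says.** Under Measurements and procedures, patients are checked at every time-point for the ability to collaborate, and "If this ability to collaborate is confirmed, a Medical Research Council (MRC) sum score assessment will also be performed". No other strength measurement is scheduled.

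Under Statistical Considerations, the score itself is analysed once, for its own course: "Changes over time in DUS markers, PMUS markers and MRC sum score will be explored using repeated-measures analysis of variance (ANOVA) or the Friedman test". The planned correlations are diaphragm marker with diaphragm marker (DUS), peripheral marker with peripheral marker (PMUS), and DUS with PMUS. None involves the MRC score. The ROC analysis concerns weaning. Strength meets the markers in one place: "In the prediction of weaning success and the presence of ICU-Acquired Weakness (ICUAW), logistic regression models will be performed". Those models use percentage change and absolute marker values, DUS and PMUS alone and combined, adjusted for covariates where available.

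The Outcomes section lists the association of elastography with the other markers, the association of DUS and PMUS changes, and the prediction of weaning. Neither strength nor ICUAW appears there. The protocol gives no ICUAW definition, no expected prevalence, and no expected number of patients with an MRC score.

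**The concern.** A yes/no state treats all patients on the same side of the cut as equally strong and separates patients who differ by one point. If ICUAW is a cut of the MRC score, the only marker-strength analysis discards the grading that the study has gone to the bedside to record. A real association is then more likely to be missed.

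Two features sharpen this. First, only patients who can collaborate are scored, and the Recruitment Procedure section expects most patients to be unable to consent at enrolment, so early scores will be scarce. Second, a logistic model is limited by the smaller of its two outcome groups. With 84 scored and a prevalence of 25%, that group is 0.25 × 84 = 21 patients; with 42 scored it is about 10 (0.25 × 42 = 10.5). The planned models put combined markers and covariates on that base. An ordinal analysis uses every distinction among the scored patients.

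**Working it through.** **Inputs from the protocol.** Correlation: "we estimated a medium effect size of 0.30" for Pearson's r. Error rate: "an alpha level of 5% and a 2-sided test". Power 80%. Sample size 84.

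**Inputs assumed.** The correlation of 0.30 is set for marker with marker and muscle with muscle; applying it to marker with strength is an assumption. Number scored: 42 to 84 (half to all). ICUAW prevalence: 25% to 75%. Strength is taken as an underlying normal variable, with one marker, no covariates and one assessment per patient.

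**1. The protocol's own figure.** n = ((1.960 + 0.842) / atanh(0.30))² + 3 = (2.802 / 0.3095)² + 3 = 84.9. The stated 84 is reproduced to within rounding. By the same approximation, power at 84 is 79.6%.

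**2. What a cut does in the ideal case.** Cutting a normal variable at prevalence p multiplies its correlation with a marker by φ(z_p) / √(p(1 − p)).
- p = 50%: factor 0.798, so r = 0.30 becomes 0.239
- p = 25% or 75%: factor 0.734, so r = 0.30 becomes 0.220

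Squared, the factors are 0.64 and 0.54. This comparison is with a perfectly continuous strength variable, which the study does not collect. It shows the mechanism, not the gain available.

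**3. The comparison that matters.** The realistic alternative is a rank analysis of a rounded score with a ceiling. Simulation used a normal marker and normal underlying strength with correlation 0.30, 20,000 data sets per number scored, and an MRC-like score with mean 45 and SD 10, rounded and capped at 60. A Spearman test on that score was compared with a likelihood-ratio test in a one-marker logistic model for strength below the cut. Monte Carlo error is at most √(0.25/20,000) = 0.35 points.

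| Scored | Spearman, capped score | Logistic, 50% | Logistic, 40% | Logistic, 30% | Logistic, 25% |
|---|---|---|---|---|---|
| 84 | 75.4% | 61.6% | 60.7% | 57.3% | 54.0% |
| 60 | 60.3% | 47.9% | 47.2% | 44.6% | 41.8% |
| 42 | 45.1% | 35.5% | 35.0% | 32.9% | 31.3% |

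Gains of the rank analysis over the cut, in percentage points:
- 84 scored: 75.4 − 61.6 = 13.8, up to 75.4 − 54.0 = 21.4
- 60 scored: 60.3 − 47.9 = 12.4, up to 60.3 − 41.8 = 18.5
- 42 scored: 45.1 − 35.5 = 9.6, up to 45.1 − 31.3 = 13.8

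The model is symmetric, so 75% prevalence behaves as 25% does.

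**4. A second score distribution.** With mean 44, SD 12, the same ceiling and 4,000 data sets per setting, prevalence ran from 25% to 75%. With 84 scored, Spearman gave 75% to 76% and the cut 54% to 62%, a gain of 13 (75 − 62) to 22 (76 − 54) points. With 42 scored, Spearman gave 44% to 45% and the cut 30% to 35%, a gain of 9 (44 − 35) to 15 (45 − 30) points. The two simulations agree; the wider ranges are reported.

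**5. Sensitivity.** With only 30 scored, Spearman gives 33.3% against 27.8% (prevalence 50%) and 24.4% (25%), a gain of 5.5 to 8.9 points. The loss also depends on r. In the ideal case of step 2 with 84 scored and prevalence 50% to 25%, it is 14 to 18 points at r = 0.20, 20 to 27 at r = 0.30, and 3 to 7 at r = 0.50.

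**The case against.** The strongest case against runs as follows. The document is an executive summary, its analysis plan is not shown, and an extra exploratory analysis is the kind of thing a plan supplies. Predicting a diagnosis properly calls for a binary model, and nothing in the protocol forbids analysing the score as well. ICUAW is not a listed outcome. The protocol does not say that ICUAW is derived from the MRC score. Nearly every input to the power figures is assumed. More regressions also add tests to a plan that already crosses many markers and time-points.

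Much of this stands, and it limits the size and importance of the point. It does not remove it. The protocol is not silent: it names the form of the outcome and the model, and that choice is less powerful than an analysis of data already in hand. The diagnostic question is kept by retaining the ICUAW model.

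Three stronger readings are tempting and are not supported.
- A reader might infer a loss of up to 26 points. At 84 scored that needs either Pearson on an ideal continuous score (80% against 54%), which is not collected, or a prevalence of 20% (75.4 − 49.7 = 25.7), outside the range assumed here.
- A reader might infer that the cut discards 36% to 46% of the information (1 − 0.64 to 1 − 0.54). That is relative to the same ideal score and overstates the loss against a capped one.
- A reader might infer that the study is underpowered. The 84 was set for correlations between markers and between muscles, it reproduces, and it does not depend on this analysis.

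**Conclusion.** The point holds as a cheap improvement to an additional analysis. The protocol links the markers to strength only through presence or absence of ICUAW, while collecting an ordinal score that no planned analysis sets against a marker.

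The gain from using the score is about 13 to 22 points of power with 84 scored and about 9 to 15 with 42 scored. These figures are conditional on a borrowed correlation of 0.30, an assumed prevalence of 25% to 75%, a one-marker unadjusted analysis, and ICUAW being a cut of the MRC score. The structural observation needs only the last of these, which is a reasonable inference because no other strength measure is scheduled. The gain shrinks if fewer patients can be scored, and no choice of analysis recovers patients who are never assessable.

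**What to change.** Under Statistical Considerations, add a sentence such as: *The association of each DUS and PMUS marker, alone and combined, with the MRC sum score will be estimated by proportional-odds regression (Spearman correlation for single markers) in all patients with an MRC assessment; the logistic model for ICUAW will be reported as a supporting clinical summary.*

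The cost is one sentence and one further regression per marker or combination, on data already collected. No patients, visits or measurements are added. There are two downsides: a few more exploratory tests, which should be labelled as such, and an effect scale that is less directly a diagnosis than an odds ratio for ICUAW. The second is the reason to keep the logistic model.

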**Recruitment Procedure**

All patients admitted to the study ICU will be screened within the first 24 hours after ICU admission; screening will be performed by investigators and the department’s research nursing team.

If eligibility conditions are met, participants (if awaken and able to collaborate) will be approached to provide informed consent within the first 24 hours. Then, data will start to be collected.

For participants not able to provide consent (the expected majority), with permission granted from the medical team in charge (a physician who is not participating in the research project, HRA, art. 30), data will be collected according to the study procedures. Participant’s consent (retrospectively) will be obtained as soon as patients regain capacity to provide consent.

In case of death or long-term disability impairing capacity to provide consent, the next of kin/legal representative will be asked to provide informed consent as soon as possible (HRO, art. 11).

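### The 84 enrolled is the zero-loss minimum for a single correlation, so the 80% power stated for each time-point does not hold at the weekly, extubation and ICU-discharge visits

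*Protocol*

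**What the plan says.** The sample size paragraph under Statistical Considerations sets the aim of finding a linear correlation "between the two US markers (SWE and one CMUS) and between the 2 muscles examined for each time-point". It assumes a Pearson correlation of 0.30 and continues: "To reach the power to identify such an association with 80% power, an alpha level of 5% and a 2-sided test", for which a minimum of 84 participants is given. The same section analyses the correlations separately at each time-point.

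Measurements and procedures gives 84 as the number of participants, so the calculated minimum is also the enrolment number. Visits take place at 24 hours, daily to day 5, then weekly ("at the end of every 7 days period"), at extubation and at ICU discharge. Study design and schedule limits assessment to the ICU stay.

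The protocol expects some patients to be lost. Recruitment Procedure provides for consent "In case of death or long-term disability impairing capacity to provide consent". It also expects most participants to be unable to consent at entry, so their consent is sought after data collection has begun. No loss rate or allowance is stated.

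**The concern.** A power calculation for a correlation counts complete pairs of measurements, not patients enrolled. Here the two numbers are equal, and the aim is attached to every visit in a schedule that follows patients with septic shock and a SOFA score of at least 8 until they leave the ICU. The number with a scan must fall along that schedule.

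The association between shear-wave elastography and the other ultrasound markers is the primary outcome. If the later correlations are read against a stated 80% power, a non-significant result at a weekly, extubation or discharge visit could be taken as evidence of no association when the visit had too few pairs to say so.

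**Working it through.** **Inputs from the protocol.** Pearson correlation 0.30 against 0; "an alpha level of 5% and a 2-sided test"; power 80%; 84 participants; no inflation. Retention by visit is not given and is assumed below.

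**Step 1: reproduce 84.** The Fisher z formula is n = ((z₀.₉₇₅ + z₀.₈₀) / atanh(r))² + 3. With z₀.₉₇₅ = 1.96, z₀.₈₀ = 0.8416 and r = 0.30, this gives n = 84.93, which rounds up to 85. The exact bivariate-normal calculation settles the one-patient difference. Given the X values, the test statistic is noncentral t on n − 2 degrees of freedom with noncentrality r/√(1 − r²) × √S, and power is averaged over S ~ χ² on n − 1 degrees of freedom:

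| Complete pairs | Exact power |
|---|---|
| 83 | 79.55% |
| 84 | 80.04% |
| 85 | 80.51% |

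So 84 is right, and it is the minimum for one test with every pair present.

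**Step 2: power with fewer pairs.** The same exact calculation is run at n = 84 × assumed retention, rounded. The detectable correlation at 80% power is tanh((1.96 + 0.8416)/√(n − 3)); for example, n = 67 gives tanh(2.8016/8) = 0.337.

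| Assumed retention | Pairs | Power for r = 0.30 | r detectable at 80% power |
|---|---|---|---|
| 100% | 84 | 0.80 | 0.30 |
| 95% | 80 | 0.78 | 0.31 |
| 90% | 76 | 0.76 | 0.32 |
| 80% | 67 | 0.70 | 0.34 |
| 60% | 50 | 0.57 | 0.39 |
| 50% | 42 | 0.50 | 0.42 |

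Up to 4 losses (n = 80) leave power within 2 points of 80%. The fifth (n = 79) takes it to 77.5%.

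**Step 3: where the schedule itself removes pairs.**

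- Weekly visits: anyone who has died or left the ICU has no later weekly scan, so the number falls along the series.
- Extubation: a patient who dies while ventilated has no such visit.
- ICU discharge: a patient who dies in the ICU has no such visit.
- Days 2 to 5: Eligibility requires an expected stay of more than 5 days and expected ventilation of more than 48 hours, and excludes palliative goals of care. These limit early losses but do not rule them out.
- 24 hours: a later refusal of consent or an unusable image can remove a pair even here, so enrolling 84 does not secure 84 pairs at the first visit.

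**The case against.** Several points on the other side deserve weight.

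- **The wording can be read more narrowly.** The reference to each time-point closes the sentence stating the aim, while the power sentence speaks of one association and of a minimum. Reading it as 80% at every visit is an inference. It is nevertheless the natural one, because the power sentence refers back to that aim and no single visit is named.
- **The study is observational.** Its primary outcome is to characterize an association, and no treatment decision hangs on the test. This stands and lowers the priority of the point.
- **The loss figures are assumptions.** This also stands. The provision about death concerns who gives consent; it shows that death is foreseen, not how many scans are lost, and earlier scans of patients who die may stay evaluable.
- **The document is headed as an executive summary.** A loss rationale may exist in fuller text. That would not alter the claim made here.

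A reader might go further in three ways that the protocol does not support. One is to infer that 84 is miscalculated; it reproduces exactly. Another is that power fails at every visit after the first; for days 2 to 5 this is not shown, since the entry criteria limit losses and a few of them cost little. The third is that power must cover finding both the marker correlation and the between-muscle correlation together; the protocol sets no such requirement. The option of Spearman's coefficient is a separate matter from loss of patients and adds nothing here.

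**Conclusion.** The point holds as a defect in the stated power and should be fixed, though it does not threaten the study. The number 84 is sound for one correlation with complete data. It does not deliver 80% at the weekly, extubation and ICU-discharge visits, where fewer than 84 pairs follow from confining scans to the ICU stay. Through day 5 the shortfall may be small.

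How far power falls cannot be taken from the protocol. It is modest if 90% of patients are retained and reaches about an even chance if half are. These figures assume a true correlation of 0.30, bivariate normality and a two-sided 5% Pearson test.

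**What to change.** Reword the sample size paragraph along these lines:

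1. State that 84 complete pairs give 80% power for a single Pearson correlation of 0.30 at one named early assessment, for example 24 hours.
2. Give the number of evaluable pairs expected at that assessment after refused deferred consent and unusable images, and the power at that number.
3. Remove the reference to each time-point from the powered claim.
4. For the weekly, extubation and discharge visits, give the expected number of pairs and the correlation detectable with it, and report those correlations as estimates with 95% confidence intervals.

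This costs wording only, and the stated power becomes less favourable. If the sponsor wants to keep 80% at the named assessment instead, enrolment would have to be 84/(1 − d) for a justified loss d: 84/0.90 = 93.3, so 94, at an assumed 10%, or 84/0.80 = 105 at an assumed 20%. The restated claim does not require this.
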